
#### Exploratory outcomes

A 10 mL venous blood sample will be collected from the patients under fasting conditions before and after the 8-week intervention. Plasma and serum samples will be stored at −80°C as required. The levels of inflammatory cytokines interleukin (IL)-1β and IL-18 will be tested using ELISA kits. The content of NOD-like receptor protein 3 (NLRP3), apoptosis-associated speck-like protein containing a C-terminal caspase recruitment domain (ASC), and cysteinyl aspartate-specific proteinase (caspase)-1 will be measured using polymerase chain reaction.

### Quality control

The Physical Activity Scale for the older adult will be used for monitoring the daily activities of all participants during the intervention period (53). Four WeChat groups will be established for the four groups to answer all participants’ questions about the disease, organize collective health education lectures intermittently, send some gifts, and maintain effective contact with them to ensure high compliance and an attendance rate of more than 85%. During the intervention period, one-on-one theoretical and practical teaching, including movements, breathing, and mind, will be provided to help the participants master all the key points of the PQ and pass the assessment conducted by a coach with 10 years of exercise experience to ensure the fidelity of the exercise training. Meanwhile, the participants will be asked to come to Shuguang Hospital for intensive exercise at least three times per week, and for other home exercises, training videos will be asked to be sent to the recorder.

To control for potential bias due to dietary factors, participants’ daily dietary patterns and the intake of nutritional supplements will be recorded using food diaries throughout the intervention period (54). These records will provide detailed information on daily food intake and supplement use, and will be analyzed together with other health behavior data to ensure that the intervention’s effects are not confounded by diet-related factors.

### Data management

The clinical trial data management database EpiData3.1 software will be used to ensure the accuracy of all data through dual person and dual recording. The database can only be accessed utilizing a unique password that only a specific researcher knows.

### Statistical analysis

An independent statistician who is not involved in outcome measurement will perform statistical analysis using SPSS software (version 24.0). All participants will be included in the intention-to-treat analyses. The multiple imputation method will be utilized to analyze missing data. Continuous data will be expressed as mean ± SD or median ± quartile interval, and enumeration data will be expressed as a relative ratio. Comparisons of baseline differences between groups will be performed using ANOVA or the Kruskal–Wallis H test for continuous variables and χ2 for categorical variables. Comparisons within each group (before and after 8 weeks of intervention) will be evaluated using a paired t-test or non-parametric test. Comparisons of endpoint differences between groups will be assessed using a 2 × 2 ANOVA (group × time) or the Kruskal–Wallis H test, with analysis of covariance applied when baseline is not uniform. In addition, a Difference-in-Difference (DID) analysis will be conducted to further assess the intervention effects while accounting for baseline differences and time trends.Multiple comparisons between the intervention arms will be performed using SNK-q test or the Nemenyi test. A *p* value of <0.05 will be considered statistically significant.

To further evaluate the discriminatory ability of each intervention in improving exercise tolerance, the area under the receiver operating characteristic curve (AUC) will be calculated for each intervention group, using the improvement in 6MWD as the classification criterion. Treatment effectiveness will be defined as an improvement in 6MWD ≥ 54 meters (minimal clinically important difference) (55). AUCs will be compared using the DeLong test with MedCalc software (MedCalc Software Ltd., Ostend, Belgium). A *p* value of <0.05 will be considered statistically significant.

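### Multiple imputation is prescribed, but the pairwise arm comparisons are given only to SNK-q or Nemenyi, which have no standard Rubin's-rules pooling

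*Protocol article*

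**What the plan says.** All of this is in the Statistical analysis section of the protocol article.

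- Analysis set: "All participants will be included in the intention-to-treat analyses".
- Missing data: "The multiple imputation method will be utilized to analyze missing data". No combining rule follows.
- Overall comparison: "Comparisons of endpoint differences between groups will be assessed using a 2 × 2 ANOVA (group × time) or the Kruskal–Wallis H test".
- Covariate adjustment is conditional on the observed baseline: "with analysis of covariance applied when baseline is not uniform".
- Supplementary model: "a Difference-in-Difference (DID) analysis will be conducted to further assess the intervention effects".
- Pairwise comparisons: "Multiple comparisons between the intervention arms will be performed using SNK-q test or the Nemenyi test".

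Two other places bear on this. The Introduction closes by hypothesising that the combination does better than either single intervention, which is a pairwise question. The Sample size calculation section uses a two-sided alpha of 0.0083 and expects 20% attrition.

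**The concern.** Rubin's rules take an estimate and its variance from each imputed dataset and combine them. A procedure fits under them if it supplies those two quantities. Nemenyi supplies differences in mean rank judged against a critical value. SNK supplies a sequence of reject or stop decisions that depends on the ordering of the sample means, and both the ordering and the stopping point can change from one imputed dataset to the next. The plan therefore fixes a missing-data method beside pairwise procedures that have no standard way to receive it.

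The pairwise comparisons are central to the trial. Four arms give 4 × 3 / 2 = 6 pairs, and 0.05 / 6 = 0.0083 is the alpha in the sample-size section, which suggests that the design had all six pairs in mind. What is at stake is the error rate of those comparisons. An analyst left without a pooled version of the named test may be drawn to run it once on a filled-in dataset.

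**Working it through.** **1. The plan's own figure.** With control SD 37.4, gains of 34.5, 32 and 38, two-sided alpha 0.0083 and power 0.80, a four-group ANOVA F test needs 26 per group (power 0.81). A two-sample t test for the difference of 38 also needs 26 (power 0.815). Attrition: 26 / (1 − 0.20) = 32.5, rounded up to 33, and 4 × 33 = 132. The stated sizes reproduce, and this point does not change them. They imply about 7 of 33 week-8 values missing per arm (21%).

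**2. Which named procedures pool.**

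| Procedure | Role in the plan | Estimate and variance to pool? |
|---|---|---|
| ANOVA (group × time) | overall | yes, through its contrasts |
| Kruskal–Wallis | overall, alternative | no; its chi-square can be combined by the D2 method |
| ANCOVA | only if baseline differs | yes |
| Difference-in-difference | supplementary | yes |
| SNK-q | pairwise | mean differences yes; step-down decisions no |
| Nemenyi | pairwise, alternative | no |
| DeLong | AUC comparison | yes (AUC difference and its variance) |

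The gap is in the two pairwise rows. Combining Kruskal–Wallis by D2 rescues only the overall test.

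**3. Size, if one completed dataset were tested as observed.** Rubin's total variance is T = W + (1 + 1/m)B, where W is the mean within-imputation variance, B the between-imputation variance and m the number of imputations. A completed-data analysis reports W alone.

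Simulation A used four arms of 33, SD 37.4, no true effect, 20% of week-8 values missing completely at random, m = 20, imputation from arm and baseline, and 2,000 trials per setting. The baseline-outcome correlations are assumed, because the document gives none.

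| Correlation | Kruskal–Wallis, one dataset | Kruskal–Wallis, D2 | ANCOVA contrast, one dataset | ANCOVA contrast, Rubin | √(W/T) |
|---|---|---|---|---|---|
| 0.3 | 0.126 | 0.049 | 0.106 | 0.050 | 0.885 |
| 0.5 | 0.123 | 0.048 | 0.102 | 0.051 | 0.886 |
| 0.7 | 0.097 | 0.045 | 0.116 | 0.058 | 0.887 |

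The Monte Carlo standard error at 5% is √(0.05 × 0.95 / 2000) = 0.005, so the pooled columns are compatible with 5%.

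Simulation B used 33 per arm with 7 missing at random, within-arm regression imputation from baseline, a t test on the completed data, and 8,000 null trials per setting.

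| Correlation | Averaged, at 0.05 | Single, at 0.05 | Averaged, at 0.0083 | Single, at 0.0083 |
|---|---|---|---|---|
| 0.3 | 11.4% | 10.2% | 3.0% | 2.8% |
| 0.6 | 9.0% | 9.5% | 2.3% | 2.5% |
| 0.8 | 7.3% | 7.3% | 1.6% | 1.5% |

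**4. Cross-check by hand.** √(26/33) = 0.888, close to the simulated 0.886, so the standard error is about 11% too small. From 0.886, W/T = 0.785 and B/W = (1/0.785 − 1) / 1.05 = 0.261. An estimate from a single imputation has variance of about W + 2B = 1.522W. The nominal cut-off of 1.96 therefore acts as 1.96 / √1.522 = 1.589, with a two-sided tail of 0.112. That agrees with the simulated 0.102 to 0.116 for the ANCOVA contrast.

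**The case against.** The strongest objection is that the text names multiple imputation, which already implies several datasets whose results are combined. The number of imputations, the imputation model and the combining rule are normally left to a statistical analysis plan, and none is shown here. This stands: those omissions are not held against the article.

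Three stronger readings are tempting, and the document supports none of them.

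- A reader might infer that the plan commits the analyst to one completed or averaged dataset. No sentence says so, and other routes exist: Kruskal–Wallis combined by D2 held its level in the check above.
- A reader might add the DeLong comparison to the incompatible tests, because it is run in separate software ("AUCs will be compared using the DeLong test with MedCalc software"). DeLong's method returns an AUC difference and its variance, which can be pooled.
- A reader might conclude that nothing in the plan pools. ANOVA contrasts, ANCOVA and the difference-in-difference model all do, and SNK-q itself starts from mean differences that have standard errors.

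It is also fair to say that the inflated error rates show the effect of treating imputed values as observed under any test, including a plain t test. They are not a property of SNK or Nemenyi.

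What survives is narrower. The protocol itself fixes the pairwise procedures, and they are the ones without a standard pooled form. A later analysis plan could not settle this by stating Rubin's rules; it would have to replace or supplement those procedures.

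**Conclusion.** The point holds as a mismatch between the chosen missing-data method and the chosen pairwise tests. It is worth correcting because the trial's hypothesis is pairwise and its alpha matches six pairwise tests.

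The numerical harm is conditional. It arises only if a completed dataset is analysed as observed, with about 20% of week-8 values missing at random and a baseline-outcome correlation between 0.3 and 0.8. Under those assumptions the false-positive rate is roughly one and a half to two and a half times the nominal 5% (7.3% / 5% = 1.5; 12.6% / 5% = 2.5). With pooled analyses it was 4.5% to 5.8%. The document does not prescribe the harmful route, so these figures show what is at risk. They do not describe the plan's own error rate.

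**What to change.** Make the primary analysis a linear model of week-8 6MWD on arm and baseline 6MWD, applied to all participants whether or not baseline looks balanced. Fit it in each imputed dataset, with arm and baseline in the imputation model. Pool the pairwise arm differences by Rubin's rules and test them at the alpha of the Sample size calculation section (0.0083). Alternatively, use a likelihood-based mixed model of the baseline and week-8 values without imputation, with the same contrasts. Keep Kruskal–Wallis and Nemenyi, if wanted, as sensitivity analyses on observed data. The DeLong comparison needs no change on this account.

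The cost is analysis wording only, since both measurements are already scheduled and the sample size does not move. Intervals will be slightly wider than those from a completed dataset treated as observed, because they carry the uncertainty due to the missing values.

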### Study design

This study is a single-center, assessor-blinded, data analyst-blinded, four-arm randomized controlled trial to be conducted at Shuguang Hospital Affiliated to Shanghai University of Traditional Chinese Medicine (TCM) in accordance with the Consolidated Standards of Reporting Trials (CONSORT) 2010 statement and the Standards for Reporting Interventions in Clinical Trials of Acupuncture (STRICTA) criteria (38, 39). A total of 132 participants will be recruited between October 2023 and October 2024, and randomly allocated to PQ exercise group (PQG), acupuncture group (AG), PQ exercise and acupuncture combined group (PAG), or control group (CG) at a 1:1:1:1 ratio. All participants will receive usual medical care and health education; those in the three intervention groups will receive PQ exercise, acupuncture treatment, or a combination of both treatments three times per week for 8 weeks. The primary outcome will be exercise endurance as assessed by a 6-min walk test (6MWT). Secondary outcomes will include lung function, degree of dyspnea, diaphragmatic function, respiratory muscle strength, skeletal muscle structure, skeletal muscle function, psychological states, and QoL. Exploratory outcomes will include the levels of inflammatory mediators. Outcomes will be measured within 1 week before and after the interventions. In addition, the frequency and severity of acute exacerbation of COPD (AECOPD) will be recorded at baseline and 1 year after intervention. A flow diagram of the study design is shown in Figure 1, and the study schedule is depicted in Table 1. This study has received ethics approval from Shuguang Hospital Affiliated to Shanghai University of TCM (approval number 2023–1360–127-01), and it has been registered in the Chinese Clinical Trial Registry (ChiCTR2300076255). The study protocol strictly follows the Standard Protocol Items: Recommendations for Interventional Trials (SPIRIT) checklist (Supplementary File 1).

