### Sample size calculation

This study is a superiority trial. The sample size was calculated on the basis of 6MWD by using PASS software (version 15.0). Based on the previous clinical studies of TCEs and acupuncture intervention for COPD (19, 40, 41), the added values of 6MWD after the intervention of TCEs, acupuncture, and exercise-combined therapy were estimated to be 34.5, 32, and 38, respectively, with the assumption that the mean value of 6MWD in the control group was 297.9 and the standard deviation was 37.4. By setting alpha to 0.0083 (two-sided) and the power to 0.80, a minimum sample size of 26 participants per group was calculated. Considering a 20% attrition rate, a total of 132 participants with 33 participants per group is a reasonable sample size for this study.

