#### Secondary outcomes

Lung function will be assessed using a spirometer (MasterScreen-Body/Diff, CareFusion Germany 234 GmbH, Germany) by a professional technician in accordance with the American Thoracic Society/European Respiratory Society guidelines (49). The outcomes include forced vital capacity, forced expiratory volume in 1 s/forced vital capacity (FEV1/FVC), predicted FEV1% (FEV1%pred), forced expiratory flow at 25% of forced vital capacity predicted (FEF25%), FEF50%, FEF75%, and maximum mid-expiratory flow after bronchodilator inhalation.The degree of dyspnea in patients will be measured using the modified Medical Research Council Dyspnea Scale, which is a 5-point scale (0–4) on which higher scores indicate worse levels of dyspnea (42).Diaphragmatic function will be evaluated by a color Doppler ultrasonic diagnostic apparatus (Aplio i900TUS-AI900, Canon, Japan) with a linear array probe (10–18 MHZ, i18LX5) in M-mode. Two experienced and trained sonographers will perform the procedure. First, the sonographer will instruct the patients to assume a seated position and place the probe at the junction of the right anterior axillary line and the 7th–9th intercostal space, ensuring that the sampling line is perpendicular to the diaphragm (50). Subsequently, precise adjustments will be made for each individual to optimize visualization of dynamic diaphragmatic images. Finally, clear and stable recordings of dynamic diaphragmatic images under resting breathing will be obtained. The diaphragm thickness at end-expiration and end-inspiration (the distance between the parallel hyperechoic medial sides of the diaphragm) and the contraction velocity of the diaphragm (displacement/time) will be measured and recorded by the sonographer. The measurements will be repeated three times, and the average value will be taken. Besides, the diaphragm thickening ratio ((mean thickness at end-inspiration – mean thickness at end-expiration)/mean thickness at end-expiration) will be calculated and recorded.The maximal inspiratory pressure (MIP) and maximal expiratory pressure (MEP) of respiratory muscle strength will be measured using a respiratory muscle strength tester (TA1, BreathHome, China). The patients will be asked to use a mouthpiece to ensure no air leakage in the mouth and nose. After breathing stably, the patients will be asked to inhale hard and quickly for more than 3 s, and the MIP will be automatically calculated by the software. After breathing stably, the patients will exhale hard and quickly for more than 3 s, and the MEP will be automatically calculated by the software. The measurements will be repeated three times with a 1-min rest interval to take the best value.Skeletal muscle structure will be measured by a color Doppler ultrasonic diagnostic apparatus (Aplio i900TUS-AI900, Canon, Japan) with a linear array probe (10–18 MHZ, i18LX5) in M-mode. First, The patients will be asked to lie in a supine position, breathe calmly, with their upper limbs extended and palms up and naturally placed at the side of the body. The probe will be placed at the middle and upper 1/3–1/2 of the starting and end points of the biceps brachii muscle to collect clear and stable images. The thickness of the soft tissue in front of the humerus and the cross-sectional area of the biceps brachii muscle will be calculated and recorded. Second, the probe will be placed at 1/2–3/5 of the distance from the anterior superior iliac spine to the upper edge of the patella to collect clear and stable images of the patient in supine position while the lower limb is extended. The thickness of the soft tissue in front of the femur and the cross-sectional area of the rectus femoris muscle will be calculated and recorded. All the above tests will be repeated three times, and the average value will be taken.Skeletal muscle function will be assessed using an isokinetic muscle strength testing system (HUMAC NORM, CSMi, American) and a wireless bio-signal acquisition system (Delsys Inc., Boston, United States) to evaluate the strength and endurance of the major skeletal muscles of the upper and lower limbs. Isokinetic muscle strength tests will be performed at slow (60°/s) and fast (180°/s) angular velocities on the elbow and knee joints separately by a technician in accordance with the manual of the instrument. At an angular velocity of 60°/second, the patients will be instructed to perform five consecutive flexion and extension exercises with their maximum effort within the designated range of motion, and peak torque will be recorded. At an angular velocity of 180°/second, the patients will be asked to complete 30 consecutive flexion and extension exercises with their maximum effort throughout the entire range of motion, and total work and fatigue index are recorded. Moreover, surface electromyography signals from two 6-s maximal static contraction tests and one exhaustive static contraction test will be collected for analysis to measure the root mean square, median frequency, and mean power frequency.The psychological states of the participants will be evaluated using the Hamilton Anxiety Scale (HAMA) and the Hamilton Depression Scale (HAMD), which will be completed through self-assessment (51). The HAMA, consisting of 24 items scored from 0 to 4, will assess anxiety symptoms. The HAMD, consisting of 24 items rated on a scale of 0–2 or 0–4, will evaluate depressive symptoms. Higher scores indicate higher levels of anxiety and depression.QoL will be assessed utilizing the St. George’s Respiratory Questionnaire, a specific assessment tool for patients with COPD (52). This questionnaire comprises a total of 50 questions that cover three main aspects: symptoms, activities, and effect on daily activities. Each question is scored on a scale ranging from 0 to 100 on the basis of its significance, with lower scores indicating no impairment and higher scores indicating extreme impairment.The frequency and severity of AECOPD 1 year before and after the intervention will be recorded.

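### Exacerbation frequency falls under the generic between-arm menu, which uses the prior-year count inefficiently or not at all; a count model that always adjusts for it would recover power at little cost

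*Protocol article*

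**What the plan says.** Under Secondary outcomes the protocol article states: "The frequency and severity of AECOPD 1 year before and after the intervention will be recorded". Study design says the same in other words: "the frequency and severity of acute exacerbation of COPD (AECOPD) will be recorded at baseline and 1 year after intervention". Table 1 lists exacerbations among the secondary outcomes, and they are the only outcome scheduled at week 60.

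The Statistical analysis section sets one rule for between-arm comparisons and exempts no outcome: "Comparisons of endpoint differences between groups will be assessed using a 2 × 2 ANOVA (group × time) or the Kruskal–Wallis H test". The sentence goes on: "with analysis of covariance applied when baseline is not uniform". The next one adds: "a Difference-in-Difference (DID) analysis will be conducted to further assess the intervention effects while accounting for baseline differences and time trends". Missing data are to be handled by multiple imputation. The significance threshold is given as "A *p* value of <0.05 will be considered statistically significant". No Poisson, negative binomial or other rate model is named, and no method uses follow-up time.

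**The concern.** Participants must be stable at entry and no minimum exacerbation history is required. Annual counts will therefore probably be small and skewed, with many zeros. The prior-year count is the obvious covariate and is already being collected. Under the stated menu it can enter in three ways:

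- as a subtracted baseline with fixed weight 1 (group × time, or DID);
- not at all (Kruskal–Wallis on the follow-up count);
- as a regression covariate, but only if the arms happen to differ at baseline.

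At stake is the precision of the trial's only one-year outcome, with 26–33 participants per arm. The form of the result matters too: a rank p-value or a difference in change of counts is harder to interpret than a rate ratio.

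**Working it through.** **1. The plan's own figure.** The protocol states: "By setting alpha to 0.0083 (two-sided) and the power to 0.80, a minimum sample size of 26 participants per group was calculated". A one-way ANOVA with means 297.9, 332.4, 329.9 and 335.9, SD 37.4 and alpha 0.0083 gives 26 per group (power 0.81). Allowing for 20% attrition, 26/0.8 = 32.5, so 33 per group, and 33 × 4 = 132. The figure reproduces, but it concerns the 6-minute walk distance only. Nothing is stated for exacerbations.

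**2. Variance of the contrasts.** Let r be the correlation between the prior-year and follow-up counts, with equal variances. Relative to the follow-up count alone (1), the change score has variance 2(1−r) and ANCOVA has 1−r². Their ratio is 2/(1+r).

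| r | change, 2(1−r) | ANCOVA, 1−r² | ratio |
|---|---|---|---|
| 0.2 | 1.60 | 0.96 | 1.67 |
| 0.3 | 1.40 | 0.91 | 1.54 |
| 0.4 | 1.20 | 0.84 | 1.43 |
| 0.5 | 1.00 | 0.75 | 1.33 |

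Below r = 0.5 the change score is worse than ignoring baseline. DID with two periods is the same contrast as group × time, so it is no remedy.

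**3. Assumed inputs (none is in the documents).** Control rate μ = 0.8 or 1.2 per year, gamma frailty variance k = 0.5 or 1.0, rate ratio 0.5 or 0.75, 26 or 33 per arm, full follow-up, one pairwise contrast, two-sided 0.05. In the control arm r = μk/(1+μk):

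- 0.4/1.4 = 0.29
- 0.6/1.6 = 0.38
- 0.8/1.8 = 0.44
- 1.2/2.2 = 0.55

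Three of the four settings lie below 0.5.

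**4. One setting by hand.** Take μ = 1.2, k = 0.5, rate ratio 0.5 and n = 33. The expected difference is 1.2 × 0.5 = 0.60.

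- Variances: prior year, and control follow-up, 1.2 + 1.44 × 0.5 = 1.92; treated follow-up 0.6 + 0.36 × 0.5 = 0.78. Covariances: 0.72 (control) and 0.36 (treated).
- Change/DID: control 2 × 1.92 − 2 × 0.72 = 2.40; treated 1.92 + 0.78 − 2 × 0.36 = 1.98. SE = √(4.38/33) = 0.364, z = 1.65, power about 38%.
- Follow-up count alone: SE = √(2.70/33) = 0.286, z = 2.10, power about 55%.
- Linear ANCOVA, always applied: common slope (0.72 + 0.36)/(2 × 1.92) = 0.281. Residual variances are 1.92 − 2 × 0.281 × 0.72 + 0.281² × 1.92 = 1.67 and 0.78 − 2 × 0.281 × 0.36 + 0.281² × 1.92 = 0.73. SE = √(2.40/33) = 0.270, z = 2.23, power about 60%.

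Simulation of this setting gave 40% for change, 52% for Kruskal–Wallis and 65% for negative binomial regression with log(prior-year count + 0.5).

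**5. Simulated power over all settings, rate ratio 0.5.**

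| Analysis | Power |
|---|---|
| Change score (group × time, DID) | 22–40% |
| ANCOVA only when baseline differs, otherwise change | 21–40% |
| Kruskal–Wallis on follow-up count | 24–53% |
| Linear ANCOVA, always | 32–63% |
| Log-link count model with baseline, always | 39–67% |

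A separate run of the negative binomial model gave 36–65%. Across runs the count model gains about 15–28 points over change/DID and about 5–25 over Kruskal–Wallis. Its null rejection rate was about 4–6% in the negative binomial form. Monte Carlo error is around ±4 points, and some negative binomial fits gave convergence warnings.

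**6. Smaller effect.** At rate ratio 0.75 the gain is about 2–8 points. One run gave 9–13% for Kruskal–Wallis, 7–13% for change and 12–18% for negative binomial.

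**The case against.** The plan does not ignore baseline. A reader might infer that group × time ANOVA and Kruskal–Wallis are the only between-arm tests. The documents do not support that, because conditional ANCOVA and DID are both written in. This stands as a correction, but neither repairs the loss: DID repeats the change contrast, and under randomisation ANCOVA will seldom be triggered.

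A reader might also infer that the normal-error model is the main fault. It is not. Linear ANCOVA, always applied, reaches 32–63% against 39–67% for the count model, so most of the gain over change/DID comes from unconditional adjustment. The count model adds a few points, uses time at risk and gives a rate ratio.

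A third tempting inference is that attrition makes the loss worse because partial-year counts would be treated as full-year counts. The plan prescribes multiple imputation, not raw partial counts. The allowance, "Considering a 20% attrition rate", belongs to the sample size for the walk test, which is measured at week 8; it is not a stated one-year loss. No power figure should rest on it.

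The article's wording could also mean Kruskal–Wallis applied to changes. That would use baseline, but no better: in a run with control rates of 1.0–1.5 and 33 per arm it had 20–40% power, against 23–44% for group × time.

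Finally, this is a condensed article and an analysis plan that is not shown may hold a count model. That limits the weight of the point. The article does, however, name the tests for endpoint comparisons without exempting this outcome, so the point concerns a stated choice and not a missing detail.

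**Conclusion.** The point holds as a worthwhile improvement to one secondary outcome. As written, the prior-year exacerbation count enters through an inefficient change score, not at all, or through an ANCOVA that depends on chance imbalance. Always adjusting in a log-link count model would gain about 15–28 points of power over change/DID and about 5–25 over Kruskal–Wallis at rate ratio 0.5, but only about 2–8 points at 0.75.

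These sizes rest wholly on the assumed rates, frailty variance and effects. The direction of the change-score result rests only on the variance formulas. Even the better model stays below 70% power at an uncorrected 0.05 in every setting tried. A reader might infer that the trial's stated power is wrong; it is not touched, since it concerns the walk distance and none is claimed for exacerbations.

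**What to change.** In the Statistical analysis section, take exacerbation frequency out of the general menu. Analyse it by negative binomial regression (log link) with arm as a four-level factor, log(prior-year count + 0.5) always included and log(observed follow-up time) as offset. Report rate ratios with 95% confidence intervals for the planned arm contrasts, and do not use the group × time or DID contrast for this outcome.

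The cost is one sentence. The covariate is already collected, the named software fits generalized linear models, and no participants, visits or procedures are added.

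The downside is possible instability if events are few. A Poisson model with robust variance and the same terms is a reasonable fallback, but its type I error reached about 9% at 26 per arm in one run. The fallback should therefore be specified with a small-sample correction.

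### The between-group model for 6MWD is written for the wrong layout (2 × 2 in a four-arm trial), and baseline adjustment depends on an undefined baseline check, which costs precision and prespecification

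*Protocol article*

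**What the plan says.** Under Study design, the protocol article describes a "four-arm randomized controlled trial", with participants allocated to Qigong, acupuncture, the combination, "or control group (CG) at a 1:1:1:1 ratio". Table 1 schedules 6MWD twice, at week 0 and week 8.

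The Statistical analysis section sets out the following steps for continuous outcomes:

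- A baseline check: "Comparisons of baseline differences between groups will be performed using ANOVA or the Kruskal–Wallis H test for continuous variables".
- The between-group comparison: "Comparisons of endpoint differences between groups will be assessed using a 2 × 2 ANOVA (group × time) or the Kruskal–Wallis H test".
- A conditional switch of model: "with analysis of covariance applied when baseline is not uniform".
- A further analysis that is not conditional: "a Difference-in-Difference (DID) analysis will be conducted to further assess the intervention effects while accounting for baseline differences and time trends".

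The section does not define what counts as non-uniform: no test level, no variable and no size of imbalance. It does not say which of these analyses decides the result for 6MWD.

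**The concern.** Two things are stated in a form that cannot be carried out as one fixed analysis.

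**Layout.** Four groups by two times is 4 × 2. Read literally, a 2 × 2 group-by-time analysis has only two groups. It would mean a set of separate two-arm analyses, which is not the same as one model with a four-level arm factor.

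**Trigger.** Baseline 6MWD can be expected to predict week-8 6MWD whether or not a baseline test is significant. In a randomised trial such a test asks whether chance produced the imbalance, which is known in advance, so it is no guide to whether adjustment is useful. Making ANCOVA depend on it leaves the choice of model for the only primary endpoint until the data are seen, by a rule that different analysts could apply differently. In most trials it also leads to the less precise analysis.

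At stake are the power of the pairwise comparisons with control and the reader's confidence that the reported model was the planned one.

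**Working it through.** **Inputs from the article (Sample size calculation).** Gains in 6MWD of 34.5 (traditional exercise), 32 (acupuncture) and 38 (combined); SD 37.4; two-sided alpha 0.0083; power 0.80; 26 per group before attrition; 20% attrition; 33 per group; 132 in total.

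**Assumed input.** The correlation r between baseline and week-8 6MWD is not in the article. The range 0.3 to 0.8 is shown. The SD of 37.4 is taken as the SD of 6MWD at each visit.

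**1. The plan's own figure.** A one-way ANOVA F-test on four groups (gains 0, 34.5, 32, 38; SD 37.4; alpha 0.0083) first exceeds 80% power at n = 26 (81%; n = 25 gives 79%). A two-sample t-test of combined versus control (38 m) also gives 26. Then 26/(1 − 0.20) = 32.5, rounded up to 33, and 4 × 33 = 132. The stated sample size reproduces.

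**2. Layout.** Four arms × two visits = 4 × 2, not 2 × 2.

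**3. Group-by-time and difference-in-differences are one contrast.** With two visits, the interaction for arm A versus control is (A at week 8 − A at baseline) − (control at week 8 − control at baseline). That is the difference in mean change, which is also the difference-in-differences estimate.

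**4. Variance of each analysis, relative to an unadjusted week-8 comparison.**

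- Change score: 2(1 − r)
- ANCOVA: 1 − r²
- Ratio of change score to ANCOVA: 2(1 − r)/[(1 − r)(1 + r)] = 2/(1 + r)

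The ratio is above 1 for every r below 1, so ANCOVA is never the less precise of the two.

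**5. Power for acupuncture versus control.** Difference 32 m, n = 26 per arm, alpha 0.0083, noncentral t with 50 degrees of freedom and critical value 2.749. The effective SD is 37.4 × √(relative variance), and the noncentrality is 32/(effective SD × √(2/26)). The degree of freedom used by the covariate is ignored.

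| r | Variance ratio 2/(1+r) | SD, change | SD, ANCOVA | Power, change | Power, ANCOVA |
|---|---|---|---|---|---|
| 0.3 | 1.54 | 44.25 | 35.68 | 45% | 69% |
| 0.5 | 1.33 | 37.40 | 32.39 | 63% | 79% |
| 0.6 | 1.25 | 33.45 | 29.92 | 76% | 86% |
| 0.7 | 1.18 | 28.97 | 26.71 | 89% | 94% |
| 0.8 | 1.11 | 23.65 | 22.44 | 98% | 99% |

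Example at r = 0.6: the change-score noncentrality is 32/(33.45 × 0.2774) = 3.45, and for ANCOVA it is 32/(29.92 × 0.2774) = 3.86. For Qigong versus control (34.5 m) at r = 0.6, power is 82.9% by change score and 91.5% by ANCOVA.

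**6. Does the check distort the result?** Four-arm trials with 26 per arm were simulated, 40,000 per scenario, with the baseline ANOVA taken at 0.05 (an assumption, since the article gives no level). About 95% of trials pass the check. Among those, the mean combined-versus-control estimate was 37.9 to 38.1 when the truth was 38, and −0.05 to 0.00 when the truth was 0. The null rejection rate of the change-score F-test at nominal 0.05 was 0.040, 0.044, 0.048 and 0.049 at r = 0.3, 0.5, 0.7 and 0.8. There is no bias, and the test is slightly conservative.

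**The case against.** The strongest reply is that baseline is not ignored when the check passes. Group-by-time uses it as a change score, and difference-in-differences is planned unconditionally. This stands, and it fixes the right comparator for the loss. Setting ANCOVA against an unadjusted week-8 test would give 63% versus 86% for acupuncture at r = 0.6. The named parametric model already reaches 76%, so the gain is about 10 points. At r = 0.8 or above the gain is negligible. Only a Kruskal–Wallis test on raw week-8 values would discard baseline, and the article does not say which values it would use.

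It can also be said that the 2 × 2 label is loose wording, that the article condenses a fuller plan, and that an analysis plan may name the primary model. Leaving the designation of a model to such a plan is normal. But the wrong layout and the conditional use of ANCOVA are rules the article states, not details it omits.

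Three stronger readings are tempting, and the document does not support them:

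- **That comparisons passing the check are biased or have inflated error.** Averaged over passing trials they are unbiased and slightly conservative. A null rejection rate of about 10–12% does appear for a two-arm, unadjusted week-8 test (33 per arm, r = 0.6 to 0.9), but only among trials with baseline p between 0.05 and 0.20, about 15% of all trials. That is a selected slice and not the named parametric model.
- **That the post hoc SNK test would halve the effect by comparing means averaged over both visits.** The article does not say that it compares such means.
- **That the within-group paired tests are offered as treatment effects.** The article does not present them that way.

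**Conclusion.** The point holds as one of layout, prespecification and precision. The stated 2 × 2 model does not fit four arms and two visits. The choice between change-score ANOVA and ANCOVA rests on an undefined baseline result. Compared with ANCOVA used always, the change-score route has 1.33 times the variance at r = 0.5 and 1.18 times at r = 0.7. For the 32 m comparison at 26 per arm and alpha 0.0083, that costs about 16 points of power at r = 0.5, 10 at r = 0.6, 5 at r = 0.7 and 1 at r = 0.8.

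These sizes rest on an assumed r, on equal SDs of 37.4 at both visits, and on the article's planning alpha. The direction does not depend on r. Neither bias in the treatment estimate nor excess type I error from the check itself is shown. The stated sample size is not in question.

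**What to change.** Name one primary analysis of 6MWD: ANCOVA of the week-8 value on arm as a four-level factor, with baseline 6MWD as covariate, fitted regardless of any baseline test. Take the pairwise contrasts, with confidence intervals, from that model.

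Delete the 2 × 2 wording and the clause that makes ANCOVA conditional. Describe baseline characteristics by arm without letting a test of them choose the model. Keep difference-in-differences and the rank tests as sensitivity analyses, and label them so.

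The cost is a change of wording, made before the analyst sees outcome data by arm. Baseline 6MWD is already scheduled for every participant, so no new data or visits are needed, and 132 participants remains the target.
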